| Objectives                | 
Principal aim:
To show that functional prognosis, at 3 months after ischemic stroke, is better for the patients mobilized out of bed early, compared to the ones progressively mobilized out of bed.
 
Secondary aims:
 
 
- To show that neurological deficits (NIHSS) observed at 7 days and 3 months after stroke are improved in the Early out of bed mobilization (EOOBM) arm.
 
- To show that the functional deficit at 7 days is better in the “early” mobilized group.
 
- To show that the level of autonomy is improved at 7 days and 3 months in the “early mobilization” group.
 
- To show that EOOBM increases the chance for the patient to be back home faster
 
- To show that the length of stay is shorter in the “early mobilized” group
 
- To assess the tolerance of the EOOBM in both groups
 
- To show that EOOBM decreases the rate of immobility related mobilization
 
- To assess the impact of the two upright positioning procedures on the post stroke fatigue at 3 months
 
 |
| # of patients required    | 400 patients                                                                                                                                                                                                                                                                                                                                                                                                                                                                                                                                                                                                                                                                                                                                                                                                                                                                                                                                                                                                                                                                                                                              |

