| Statistical analyses | 
Primary outcome:
 
Percentage of the patients with a Rankin score [0-2] at 3 months will be compared between the two groups by a Chi square test.
 
If the test is not significant, a switch to a non inferiority will be performed. Bilateral confidence interval (CI) of 95% will then be calculated, and the inferior border of the CI will be compared to the non inferiority threshold of -5 %
 
A multivariate logistic regression model will be used in a second step to adjust on age and former (before the qualifying event) Rankin score.
 
Secondary outcomes:
 
 
- Clinical score (neurological deficit) based on the NIHSS at 7 days and 3 months: comparison of the mean scores between the two groups using a Student's test.
 
- Functional scale (Rankin score) at 7 days: comparison of the proportions of patients with a score [0-2] by a Chi square test.
 
- Autonomy scale (Barthel index) at 7 days and 3 months: comparison of the proportions of patients with a score < 60 (dependent) between the 2 groups using a Chi square or a Fisher test
 
- Length of stay: comparison of the means between the two groups using a Student's test
 
- Percentage of patients back at home before 7 days or 3 months: Chi square test or Fisher test.
 
- Side effects associated with sitting in the two groups (tolerance of upright positioning in the early versus progressive arms): description of the side effect in the 2 groups and comparison of the most frequent (>5%) by a Chi square test or a Fisher test.
 
- Prevalence of swallowing disturbance, pneumopathy, acute urinary retention, bladder catheterization, deep vein thrombosis during hospitalization: comparison between the two groups using a Chi square test or a Fisher test.
 
- Prevalence of post stroke fatigue: comparison between the two groups using a Chi square test or a Fisher test.
 
 
A multivariate logistic regression model will be used in a second step to adjust on age and former (before the qualifying event) Rankin score.
 |

|  |  |
|--|--|
|  |  |
|--|--|

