### **2.2. SECONDARY AIMS AND EVALUATION CRITERIA**

#### **2.2.1. Secondary aims**

To show that neurological deficits observed at 7 days and 3 months after stroke onset are improved in the « early sitting » group.

To show that the functional prognosis at 7 days after stroke onset is improved in the « early sitting » group.

To show that autonomy is improved at 7 days and 3 months in the « early sitting » group

To show that early sitting facilitates the process of going back home

To show that the length of stay is shorter in the « early sitting » group

To show that early sitting decreases the rate of complications related to immobilization.

To explore the tolerance of upright positioning in the two groups

To explore the prevalence of fatigue at 3 months after stroke in both groups.

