#### **2.2.2. Secondary outcomes**

Clinical score (neurological deficit) using the NIHSS at 7 days and 3

Functional scale (modified Rankin score) at 7 days

Autonomy scale (Barthel score) at 7 days and 3 months

Percentage of patients back home at 7 days and 3 months

Length of stay

Prevalence of swallowing disturbances, pneumopathy, urinary tract infection, bladder catheterization, deep vein thrombosis during hospitalization

Side effects of upright positioning in the two groups= tolerance of early sitting (prevalence of side effects)

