### 7 day visit (or before exiting the hospital if before D7)

Will be documented:

- Clinical data

- NIHSS
- Rankin score
- Barthel score

Exit of the hospital:

- Cause of the cerebral infarction, if available
- Internal carotid artery status (ultra sounds)
- Date
- Orientation of the patient (back home, rehabilitation, ...)
- Immobility related complications during hospitalization

3 month visit

Will be documented:

- Clinical data
  - NIHSS
  - Rankin score
  - Barthel score
- Cause of the cerebral infarction
- Presence/Absence of post stroke fatigue
- Synthesis about complications that occurred during the hospital stay

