#### Secondary outcome

- Clinical score (neurological deficit) based on the NIHSS at 7 days and 3 months: comparison of the mean scores between the two groups using a Student's test.
- Functional scale (Rankin score) at 7 days: comparison of the proportions of patients with a score [0-2] by a Chi square test.
- Autonomy scale (Barthel index) at 7 days and 3 months: comparison of the proportions of patients with a score < 60 (dependent) between the 2 groups using a Chi square or a Fisher test
- Length of stay: comparison of the means between the two groups using a Student's test
- Percentage of patient back home before 7 days or 3 months: Chi square test or Fisher test.
- Side effects associated with sitting in the two groups (tolerance of upright positioning in the early versus progressive arms) : description of the side effect in the 2 groups and comparison of the most frequent (>5%) by a Chi square test or a Fisher test.

- Prevalence of swallowing disturbance, pneumopathy, acute urinary retention, bladder catheterization, deep vein thrombosis during hospitalization: comparison between the two groups using a Chi square test or a Fisher test.
- Prevalence of post stroke fatigue: comparison between the two groups using a Chi square test or a Fisher test.

A multivariate logistic regression model will be used in a second step to adjust on age and former (before the qualifying event) Rankin score.

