### **6.2.2. Statistical justification for the number of patients required**

In a meta-analysis of two pilot studies comparing an « early » to a « usual » mobilization procedure, Craig and coll. (9) showed that the percentage of patients with a Rankin score [0-2] was 34.7 % at 3 months in the « usual » group (n=49) versus 57.4 % in the « early » group (n=54).

In our study, we hypothesized that the functional outcome at 3 months assessed by the Rankin score will be better in the « early » group than in the « progressive » group, with a percentage of Rankin [0-2] of 35% in the « progressive » group and 50% in the « early » group. With an alpha risk of 5% and a power of 80% (bilateral), 183 patients per group are required to show a difference. Total number will then be 366 patients.

Percentage of poor tolerance during the first sitting is estimated between 5 and 10% in the 2 groups. As this may affect the Rankin score at 3 months, the number of patient to include has been increase to 400.

If the superiority of the « early » group is not statistically demonstrated, a switch to non inferiority could be undertaken. For this analysis, the non inferiority threshold is set at -5 % (maximum acceptable clinical difference). With 400 patients, non inferiority will be demonstrated if the real difference between the two groups is between 9 and 15%.

Reference: Committee for Proprietary Medical Products (CPMP). Points to consider on switching between superiority and non inferiority. 2000. European Medical Agencies (AMEA). CPMP/EWP/492/99.

The study will be undertaken in 11 centers. Each one, has the potential to recruit patients, with at least 300 cerebral infarction cases a year.

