#### **6.2.5. Missing, unused and invalid data**

In the situation of a side effect requiring the patient to lie down immediately, or in case of patient death, the Rankin score will be set in the [3-5] interval at 3 month (penalized).

No imputation will be performed on the secondary outcome parameters.

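### Return home is listed as a status at 7 days and 3 months but analysed as a return before those times, and the listed data items cannot supply the 3-month figure

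*Protocol*

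**What the plan says.** The outcome appears in four places in the Protocol.

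- Outcome lists (Abstract, Secondary outcomes; section 2.2.2): "Percentage of patients back home at 7 days and 3 months".
- Analysis, Abstract (Statistical analyses): "Percentage of patients back at home before 7 days or 3 months: Chi square test or Fisher test".
- Analysis, body (section 6.2.1, Secondary outcome): "Percentage of patient back home before 7 days or 3 months: Chi square test or Fisher test".

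The aims behind it are also worded in two ways. The Abstract has "To show that EOOBM increases the chance for the patient to be back home faster"; section 2.2.1 has "To show that early sitting facilitates the process of going back home", with no time point.

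On data, section 5.2 records at hospital exit the date and "Orientation of the patient (back home, rehabilitation" among other destinations. Its list for the 3-month visit covers NIHSS, Rankin, Barthel, cause of the infarct, fatigue and a summary of in-hospital complications. It has no place of residence, and neither does the M3 column of the study schedule table. Living location is listed at the inclusion visit only. Section 6.2.5 penalises death for the Rankin score and otherwise says "No imputation will be performed on the secondary outcome parameters".

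**The concern.** A status on a date can be lost again; an event by a date, read literally, cannot. The lists and the analysis therefore describe different variables, and the split is the same in the Abstract and the body, so it is not one isolated slip. The trial is open and expects shorter stays in the early arm. A count of any return home partly repeats length of stay, while a count of patients at home on the date measures whether the return lasted.

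The second problem is practical. If the only residence information after inclusion is the destination at exit, the 3-month figure will in effect be a discharge-destination figure, whichever wording is chosen.

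**Working it through.** **Plan's own figure.** None exists for this outcome. The only sample-size figure, "With an alpha risk of 5% and a power of 80% (bilateral), 183 patients per group are required to show a difference", is for the Rankin score at 35% versus 50%. It reproduces with the continuity-corrected two-proportion formula (183 per group; 170 without the correction) and does not depend on this point.

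**How each definition classifies patients**

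| Patient | Home *at* month 3 | Home *before* month 3 (literal) | Exit record as listed |
|---|---|---|---|
| Home on day 5, still home at month 3 | yes | yes | home |
| Home on day 5, then dead, readmitted or institutionalised at month 3 | no | yes | home |
| To rehabilitation on day 10, home in week 6, still there at month 3 | yes | yes | rehabilitation |

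The second row is where the two definitions part. In the third row they agree, but the listed data miss the return home under both. At day 7 the definitions differ only for discharge on day 7 itself, or for death or readmission within days of going home.

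**Size at month 3.** All rates below are assumptions; 200 per arm is the planned 400 divided equally.

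- Gap per arm = (share ever home) × (share of those later lost). At 60% and 5%: 0.60 × 0.05 = 0.03, which is 3 points or 6 patients.
- Range for 40–70% ever home and 2–10% later lost: from 0.40 × 0.02 = 0.8 points (1.6 patients) to 0.70 × 0.10 = 7.0 points (14 patients).
- Between arms, equal loss among equal numbers sent home cancels. With 60% home in both arms and 8% versus 3% of those later lost, the contrast moves by 0.60 × (0.08 − 0.03) = 0.03, or 3 points.
- Standard error of the difference at 60%: √(2 × 0.6 × 0.4 / 200) = 0.049. The shift is 3 / 4.9 ≈ 0.6 standard errors.
- With a wider spread of 10% versus 2% later lost, the contrast moves by 0.40 × 0.08 = 3.2 points to 0.70 × 0.08 = 5.6 points.

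**The case against.** The strongest reply is that *before* is loose wording, in a text that is loose elsewhere. The NIHSS line in both outcome lists breaks off without its time unit, and urinary tract infection in the outcome list becomes urinary retention in the analysis. Section 6.2.6 also promises an analysis plan before database freeze, which could settle how later events are counted. This may well be so, but the Protocol still states two variables for one outcome, and an analysis plan cannot recover residence data that were never collected. The electronic case report form might hold a residence item that the Protocol does not list; that cannot be excluded, but the lists do not require one.

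Three stronger readings are tempting and not supported.

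- *Deaths and readmissions after discharge count as successes.* That follows from reading *before* literally, but no section states such a counting rule.
- *The analysis wording is the wrong one.* The Abstract's aim of getting home faster fits a return by a given time at least as well as a status on the date. The documents do not decide between them.
- *An arm that discharges too early would be flattered overall.* The primary outcome is the 3-month Rankin score, with death penalised in section 6.2.5, so the intention-to-treat analysis would show such harm. The per-protocol analysis, which excludes the deceased, is less protective.

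A larger effect, 5 points or about one standard error, appears if 8% and 3% are taken as shares of the whole arm. That is a different base: with 60% home it means 0.08 / 0.60 ≈ 13% and 0.03 / 0.60 = 5% of those sent home.

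**Conclusion.** The inconsistency is real and repeated, and the 3-month status that the outcome lists promise cannot be derived from the data items as listed. The consequence is small. It concerns the month-3 half of one secondary outcome; day 7 is barely affected. On the assumed 60% and 5%, the definitions differ by 3 points per arm (0.8 to 7.0 over the range shown). The between-arm comparison moves only if later loss differs by arm: by 3 points, about 0.6 standard errors, for 8% versus 3% of those who went home. All of these rates are assumptions, because the Protocol gives none for return home. The gap in data collection matters more than the preposition, since it affects either definition.

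**What to change.** Use one definition in all four places (Abstract, Secondary outcomes and Statistical analyses; sections 2.2.2 and 6.2.1), and collect what it needs.

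- **If the listed outcome (*at*) is kept:** analyse the proportion alive and living at home on day 7 and on the date of the 3-month visit, with deaths counted as not home and all randomised patients in the denominator. Change the two analysis passages. Add one line for residence and vital status to the 3-month visit in section 5.2 and to the M3 column of the schedule table. Rankin category 6 should already identify deaths, so residence is the item really missing.
- **If return by a given time is intended, as the Abstract's aim suggests:** change the two outcome lists instead. Record the date of first return home, including after rehabilitation, and state how a later death or institutionalisation is counted.

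Either way the cost is a wording amendment and one extra data line at a visit that already takes place. It is cheap to add before those visits happen and hard to recover afterwards.

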#### ➤ Risks associated with the procedure studied

Major side effects could be observed:

- Neurological worsening defined by aggravation of the existing deficits (motor, aphasia,..) or occurrence of new neurological deficits during or within the first 5 minutes after upright positioning.
- Fall that can be complicated by fracture

A complete list of the side effects can be found in the vigilance section (see infra).

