#### **5.1.2. Description of the techniques used**

Early sitting: After an initial stage (the day of stroke onset) of lying with the upper body inclined at 30° maximum, the patient is seated out of bed at the earliest time, for a minimum duration of 15 minutes, under the supervision of the physiotherapist or the nurse. Sitting can be extended up to 60 minutes, if the tolerance is good. Blood pressure and heart rate will be recorded, before, immediately and 5 minutes after upright positioning. Sitting will be repeated everyday according to the same criteria, but the duration will be decided by the staff in charge.

Progressive sitting: After an initial stage (the day of stroke onset, D0) of lying with the upper body inclined at 30° maximum, the patient is seated in bed at 45 degrees (D1), then at 60 degrees (D2). The patient is not seated out of bed before the third day after stroke (D3), for a minimum duration of 15 minutes, under the supervision of the physiotherapist or the nurse (depending of the unit organization). Blood pressure and heart rate will be recorded, before, immediately and 5 minutes after upright positioning. Sitting will be repeated everyday according to the same criteria, but the duration will be decided by the staff in charge.

Supervision during the procedure : Any side effect that led to ceasing the procedure will be noted, for example neurological worsening (degradation of the current state or occurrence of new signs), persistent blood pressure surge (increase of 40mmHg so that the BP rises above 180/100), vagal reaction (bradycardia, nausea, sweat) or hypotension . Close neurological monitoring by the staff is required during the first 5 minutes of the sitting procedure.

Slighter side effects won't lead to the ceasing of the procedure: bearable headache, isolated nausea or vomiting.

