### Early sitting (D1 or D3 according to the group)

- Tolerance, potential side effects
- Blood pressure, heart beat, before, immediately and 5 minutes after upright positioning
- Duration of the upright positioning

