### **5.3. IDENTIFICATION OF THE DATA COLLECTED OUTSIDE OF THE MEDICAL FILE**

- Blood pressure and heart rate during the sitting procedure
- Tolerance of the first sitting, with collection of any related side effect
- Barthel score at inclusion time, D7 (or last day of hospital) and 3 months
- Rankin score at inclusion time, D7 (or last day of hospital) and 3 months

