## **7.2. LIST OF THE EXPECTED EVENTS OR SIDE EFFECTS**

### **Associated with the procedure tested:**

Common undesired events for the « early » and the « progressive » procedures:

In this case the causation of the event by the procedure is considered if it occurs within the first minutes after it started. Outside of this temporal definition, the undesired event will be associated with the evolution of the disease.

- Nausea/Vomiting
- Headache
- Neurological worsening (aggravation of the existing deficits or occurrence of new ones)
- Blood pressure surge persistent on a second measurement, with a BP increase of at least 40mmHg and above 180/100
- Sensation of passing out (linked to a vagal reaction (bradycardia, nausea, sweating) / Hypotensive / other)
- Fall that can be associated with traumatic brain injury or other orthopedic complications (fracture, luxation, sprain)

« Progressive arm »: Complications linked to immobility

- Deep vein thrombosis,
- Pneumopathy
- Urinary tract infection,
- Constipation,
- Sores,
- Swallowing disturbances

“Early arm” Neurological worsening (aggravation of the existing deficits or occurrence of new ones)

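### Neurological worsening, the named main risk, is targeted only by a sitting-tolerance comparison that covers minutes on different days and tests only effects above 5%

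*Protocol*

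**What the plan says.** Protocol 1.2.3 calls neurological worsening the main risk and notes that it can arise in the natural course of stroke without any mobilisation. Four parts of the protocol decide how it enters a comparison of the arms.

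- **Window.** The section on risks of the procedure counts worsening that occurs "during or within the first 5 minutes after upright positioning". Section 7.2 likewise accepts causation only in the first minutes and adds: "Outside of this temporal definition, the undesired event will be associated with the evolution of the disease". Section 7.2 also lists worsening separately for the early arm, with no window, so the text is unclear there.
- **Timing.** The schedule in 5.2 records tolerance at "Early sitting (D1 or D3 according to the group"), and 5.3 lists "Tolerance of the first sitting, with collection of any related side effect". Section 5.1.2 is wider: "Any side effect that led to ceasing the procedure will be noted, for example neurological worsening" is not limited to the first sitting.
- **Test.** The item in 6.2.1 is "Side effects associated with sitting in the two groups (tolerance of upright positioning in the early versus progressive arms"). It describes side effects in both groups, then plans a "comparison of the most frequent (>5%) by a Chi square test or a Fisher test".
- **Expected frequency.** Section 6.2.2: "Percentage of poor tolerance during the first sitting is estimated between 5 and 10% in the 2 groups".

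Section 6.2.1 also compares five named complications over the hospital stay. Neurological worsening is not one of them.

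**The concern.** Because worsening also occurs spontaneously, judging cause patient by patient cannot show whether early sitting adds to it. That needs a count by randomised arm over roughly the same days, whatever the presumed cause.

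The tolerance item does something else. It leaves out early-arm worsening that begins hours after sitting, and progressive-arm worsening on D1 or D2. It sets D1 in one arm against D3 in the other, when background risk may differ. The 5% rule may also mean that worsening is never tested.

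At stake is a question any clinician will ask of the results: did more patients worsen in the first week when seated early?

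**Working it through.** **Plan's own figure.** For 35% against 50%, two-sided 5% and 80% power, the continuity-corrected two-proportion formula gives 183 per group, as in 6.2.2. Nothing below disputes that number. With 400 patients there are 200 per arm.

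**1. The 5% rule.** If worsening is a share s of poor tolerance, its rate is s × 5% to s × 10%. Even at the 10% end, s must exceed one half for the expected rate to pass 5%. The protocol gives no value for s, so it is varied. Nor does it say whether 5% is pooled or per arm, so both are shown: pooled is P(X > 20) for Binomial(400, p); either arm is 1 − P(X ≤ 10)² for Binomial(200, p).

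| Worsening rate p | Example | Pooled above 5% | Either arm above 5% |
|---|---|---|---|
| 1.25% | s = 1/4 of 5% | 0.0% | 0.0% |
| 2.5% | s = 1/4 of 10%, or 1/2 of 5% | 0.1% | 2.5% |
| 3.75% | s = 3/4 of 5% | 7.9% | 24.9% |
| 5% | s = 1/2 of 10% | 44.1% | 66.0% |

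**2. The comparisons that ignore cause.** Assume 5% against 10% worsened by D7. The protocol gives no rate.

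- *NIHSS t-test.* Suppose worsened patients rise by 6 points and the others improve by 2, a gap of 8. The mean shift is 0.05 × 8 = 0.4. The standard error is SD × √(2/200): 0.4, 0.5 and 0.6 for SD 4, 5 and 6. Power is about 17%, 13% and 10%. Patients who die have no NIHSS, and 6.2.5 rules out imputation for secondary outcomes, so deaths leave this test.
- *D7 Rankin 0-2 and Barthel below 60.* As an upper bound, let every extra worsened patient cross the threshold, a 5-point shift. Power is 17 to 22% for Rankin (base 25 to 50%) and 17 to 19% for Barthel (base 30 to 50%).

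**3. A direct count (NIHSS rise of at least 4, or death).** With observed rates of 5% and 10%, power is 47.5%. The 95% half-width is 1.96 × √(0.05 × 0.95/200 + 0.10 × 0.90/200) = 1.96 × 0.0262 = 5.1 points.

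That assumes almost nobody else crosses the cut-off. Let the others change by −2 on average with the SD below. NIHSS is a whole number, so a rise of at least 4 corresponds to 3.5 on a continuous scale. The false-positive rate is f = P(Z > 5.5/SD), and the observed rates become 5% + 95% × f and 10% + 90% × f.

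| SD of change | f | Observed rates | Power | Half-width |
|---|---|---|---|---|
| 1.5 | 0.0% | 5.0% vs 10.0% | 48% | 5.1 |
| 3 | 3.3% | 8.2% vs 13.0% | 35% | 6.0 |
| 4 | 8.5% | 13.0% vs 17.6% | 24% | 7.0 |

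So 48% is near a best case. Recovery before the assessment lowers it too: in a simulation with SD 1.5, 50% recovered by D7 and 20% of the rest dead, power was about 26%.

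**The case against.** The strongest reply is that this is an omission, not an error. Tolerance of sitting has to be recorded when the patient sits, so D1 against D3 follows from the intervention, and the protocol does not claim that this item measures all worsening. A cut on NIHSS could be left to the analysis plan foreseen in 6.2.6. Part of this stands: the item is reasonable for tolerance. But the attribution window, the D1/D3 recording and the 5% rule are fixed in the protocol, and together they form the only comparison directed at the risk it calls main.

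A reader might infer that the protocol never compares worsening between arms, or leaves it unwatched. The documents do not support that. D7 and 3-month scores compare the arms regardless of cause. All side effects are described by arm; only the test is restricted. Collected parameters are described in both groups (6.2.1) and unexpected events documented (7.1.1). Death, or a side effect that forces the patient to lie down, counts as failure on the primary outcome (6.2.5). A safety committee exists (7.3.2), and 5.4.3 allows early stopping for harm. Nor is recording confined to the first sitting, given 5.1.2.

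Two criticisms of the remedy also stand. D7 or exit is not strictly one window, since the protocol hopes for shorter stays in the early arm. And dropping the 5% rule alone would gain little, because a test at such low rates has little power.

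**Conclusion.** The point holds as a minor one. The comparison aimed at the named main risk depends on attribution within minutes, mainly sets D1 against D3, and may never be tested. The other comparisons reflect lasting worsening indirectly, without counting worsened patients.

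For an assumed 5% against 10% with 200 per arm, a direct count has about 24 to 48% power, against 10 to 17% for the NIHSS t-test. The rates, the 6-point rise, the 2-point improvement and the SDs are assumptions; only the 5% rule, the 5 to 10% tolerance estimate and the sample size come from the protocol. The gain in power is modest. The main benefit is an interval for the question clinicians will ask. The primary analysis is unaffected.

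**What to change.** Add one safety comparison to 6.2.1, by randomised arm and regardless of attribution: the proportion of patients with an NIHSS rise of at least 4 points from inclusion to the D7 or exit assessment, or death by D7.

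Report:
- the risk difference with its 95% confidence interval;
- the day of assessment by arm;
- the number of survivors without a D7 or exit NIHSS, with a sensitivity analysis counting them as worsened.

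State the limits:
- the 4-point cut-off is a proposal (the exclusion criteria use 4 points only for fluctuating deficit);
- exit before D7 may be more common in the early arm, so the window is only approximately common;
- worsening that recovers before the assessment is missed;
- the interval is to be read, and a non-significant result is not proof of safety.

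Keep the existing NIHSS, Rankin, Barthel and tolerance analyses. The cost is one more secondary analysis. NIHSS is already taken at inclusion and at D7 or exit, and deaths are already reported, so no new visit or data item is needed.

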## 1.2.3. Risk-benefit ratio

The main risk of the study relies on the possibility of neurological worsening, a side effect that can spontaneously occur during the disease natural history, even without any mobilization of the patient. The physician may be fearful of this outcome, which usually leads to a more prolonged immobility for the patient. It increases the length of stay and the risk of complications (urinary

tract infection, constipation, deep vein thrombosis...), and also delays the ability to return to the former level of autonomy. Data from literature, even though incomplete, don't seem to show that EOBBM is associated with a poor outcome. Risks that are taken in this study regarding neurological worsening are therefore low, for a potential benefit at the population scale, improving patient outcome, but also alleviate the socio economic burden of stroke.

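### The >5% filter can leave neurological worsening and falls, the harms the protocol ranks highest, described by arm but never formally compared, and the base of the 5% is not defined

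*Protocol*

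**What the plan says.** Tolerance of upright positioning is a secondary outcome (Protocol 2.2.2). For its analysis, section 6.2.1 provides a "description of the side effect in the 2 groups" and then a "comparison of the most frequent (>5%) by a Chi square test or a Fisher test". The abstract repeats the rule. Neither place says whether 5% refers to all patients, to each arm or to either arm, and no event is exempt.

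Three other places bear on which events the rule reaches:

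- Section 1.2.3 states: "The main risk of the study relies on the possibility of neurological worsening". Section 1.2.2.1 lists worsening first of two major side effects of the procedure; the second is "Fall that can be complicated by fracture". Section 7.2 lists worsening again, separately, for the early arm.
- Section 6.2.2 states: "Percentage of poor tolerance during the first sitting is estimated between 5 and 10% in the 2 groups". It gives no breakdown by type of event.
- Section 5.1.2 states: "Any side effect that led to ceasing the procedure will be noted, for example neurological worsening". Its other examples are a blood pressure surge, a vagal reaction and hypotension. It separates milder events: "Slighter side effects won't lead to the ceasing of the procedure: bearable headache, isolated nausea or vomiting".

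**The concern.** The rule chooses events for comparison by how common they are, not by how much they matter. The events the protocol ranks as major may be too rare to pass a 5% cut when all poor tolerance at the first sitting is expected in only 5-10% of patients. The same section tests immobility complications, the harms that section 7.2 attaches to the progressive arm, with no frequency cut. The harm listed specifically for the early arm is tested only if it is common.

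At stake is the tolerance conclusion. An excess of worsening in the early arm could appear in a descriptive table with no estimated difference, interval or test. Because the base of the 5% is open, whether some imbalances are tested could also be settled after the counts are known, in a trial that section 3.1 describes as open.

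**Working it through.** **Inputs.** 400 patients, 1:1, so 200 per arm (sections 4.1 and 6.2.8). Poor tolerance at first sitting 5-10% (6.2.2). Cut >5% (6.2.1). The share of poor tolerance due to worsening is not in the protocol and is varied below as an assumption.

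**The plan's own figure.** For 35% versus 50%, two-sided 5%, power 80%, the two-proportion formula with continuity correction gives 183 per group, as section 6.2.2 states (170 without the correction). The basis for 200 per arm is therefore not in question.

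**What the cut requires.** Pooled: more than 0.05 × 400 = 20, so at least 21 patients with the event. Per arm: more than 0.05 × 200 = 10, so at least 11 in an arm. A pooled rate above 5% implies that at least one arm is above 5%, so the either-arm reading is the most permissive.

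**Share needed.** For a true rate above 5%, worsening must exceed 5/10 = 50% of a 10% total or 5/7.5 = 67% of a 7.5% total. With a 5% total, even a share of 100% only reaches 5%.

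**Chance of being tested, equal rates in both arms.** With p = total × share:
- pooled: P(X ≥ 21), X ~ Binomial(400, p)
- either arm: 1 − [1 − P(Y ≥ 11)]², Y ~ Binomial(200, p)

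| Total | Share (assumed) | p | Pooled | Either arm |
|---|---|---|---|---|
| 10% | 25% | 2.5% | 0.1% | 2.5% |
| 10% | 33% | 3.3% | 2.9% | 14% |
| 10% | 50% | 5.0% | 44% | 66% |
| 10% | 75% | 7.5% | 97% | 99% |
| 7.5% | 33% | 2.5% | 0.1% | 2.5% |
| 7.5% | 50% | 3.75% | 8% | 25% |
| 7.5% | 75% | 5.6% | 66% | 82% |
| 5% | 50% | 2.5% | 0.1% | 2.5% |
| 5% | 100% | 5.0% | 44% | 66% |

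**Chance of being tested when the early arm is worse (assumed rates).** 5% versus 1%: 1% pooled, 42% either arm. 6% versus 2%: 13% and 66%. 8% versus 2%: 44% and 93%.

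**Imbalances that the rule leaves uncompared.**

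- 10/200 versus 2/200: pooled 12/400 = 3.0%, larger arm exactly 5.0%, which does not exceed 5%. Difference 4.0 points; SE = √(0.05 × 0.95/200 + 0.01 × 0.99/200) = 0.0169; 95% CI 4.0 ± 1.96 × 1.69 = 0.7 to 7.3 points; Fisher p = 0.036. Not tested under either reading.
- 9/200 versus 1/200: pooled 2.5%, larger arm 4.5%; Fisher p = 0.020. Not tested under either reading.
- 14/200 versus 4/200: pooled 18/400 = 4.5%, larger arm 7.0%. Difference 5.0 points, SE 0.0206, 95% CI 1.0 to 9.0; Fisher p = 0.027. Not tested if the 5% is pooled, tested if either arm counts. Here the undefined base alone decides.

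**The case against.** The rule is less bare than the second half of its sentence suggests. All side effects are described in both groups, and 6.2.1 requires numbers and percentages for every collected variable, so a reader will see worsening and falls by arm. Worsening also enters tested outcomes: mean NIHSS at 7 days and 3 months has no frequency cut, and under 6.2.5 a side effect that forces the patient to lie down at once counts as a poor Rankin result in the primary analysis. Describing all events and testing only frequent ones is a recognised safety-reporting choice. A test would also have limited power: at 200 per arm, about 37% for 5% versus 2%, 49% for 4% versus 1%, 53% for 6% versus 2% and 65% for 5% versus 1%. An analysis plan is due before database freeze (6.2.6).

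Most of this stands, and it limits the point. It does not remove it. A mean NIHSS dilutes an event in a few percent of patients, and the penalised Rankin score mixes it with death and every other cause of disability, so neither estimates the between-arm difference in worsening. The filter is also fixed in the protocol itself, so this is not a detail left for later.

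A reader might go further and infer that worsening will probably never be compared, by spreading the 5-10% over the six event types of section 7.2. The documents do not support that. They give no split by type. The figure concerns the first sitting, whereas sitting is repeated daily, so it is not a strict ceiling. The mild events in 5.1.2 may not count as poor tolerance at all, which would raise the share due to worsening.

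**Conclusion.** The point holds as a weakness in the comparison rule, not as a claim that harm will go unreported. The events ranked as major may well fall below the cut. With equal arms, a worsening share of a third or less of poor tolerance gives at most about a 3% (pooled) or 14% (either-arm) chance of a test. A test becomes about as likely as not, or better, only if worsening is half or more of a 10% total, a larger share of a lower total, or concentrated in the early arm under an either-arm reading. These probabilities rest on assumed shares and on applying the first-sitting figure to the filtered rate.

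The examples with 10 versus 2 and 9 versus 1 events need no assumed share: a nominally significant excess can go uncompared whichever base is used. It would be inaccurate to conclude that the tolerance claim would rest on minor events only, since major events stand in the same descriptive tables. What may be missing is the estimated difference, its interval and the test.

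**What to change.** In section 6.2.1 and the matching abstract row, state that neurological worsening and falls during sitting are always compared between arms whatever their frequency, with the risk difference, its 95% confidence interval and a Fisher test. Keep the >5% rule for the other side effects, and say whether 5% is pooled or reached in either arm.

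The cost is a sentence or two in each place. No new data are needed, since side effects are already collected by arm. The intervals will be wide for rare events. Given the power figures above, the text should add that a non-significant result is not evidence of no harm, and that the interval carries the interpretation.
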